### Statistical analyses

2.8

Unless otherwise specified, a two-sided 0.05 level of significance will be used to declare treatment arms significantly different. Intention-To-Treat analyses will be conducted. All statistical analyses will be performed using SPSS for Windows (version 25.0.0.2) or other widely accepted statistical or graphical software.

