#### Power and sample size calculation

2.8.1

For the sample size calculation, a medium effect size of 0.57 was assumed, which is similar to the effect size for symptom severity detected in the most recent meta-analysis and the effect size for cognition [36,37]. Sample size calculation was based on disjunctive power (or minimal power), which is the probability of finding at least one true intervention effect across all of the outcomes. To be able to find an effect size of 0.57, with two sided alpha set at 5% and with 80% power, 50 participants in each group have to be evaluated. Since we expect some 10% dropout, a total of 55 participants per arm are needed, resulting in a total of 110 participants.

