#### Primary study parameters

2.8.2

The primary analysis will include change in psychotic symptoms as measured by the PANSS at 6 and 12 weeks of treatment (end-of-treatment) and at 6 months after end of treatment and change in cognitive functioning as measured by the BACS at 12 weeks of treatment (end-of-treatment) and at 6 months after end of treatment. A mixed model for repeated measurements will be used, including at least time point, treatment group, the interaction between time point and treatment, sex and age as fixed factors, baseline PANSS/BACS-score, concomitant antipsychotic medication which will be converted to mean daily olanzapine equivalent dose [47], current drug and alcohol use as covariate and subject as random intercept factor. More specifically, the primary analysis will be a repeated measures analysis of variance (ANOVA) with time as within factor (baseline, 6 weeks and 12 weeks of treatment) and treatment as between factor (raloxifene or placebo), with symptom severity (PANSS total, positive, negative or general scores) as dependent variables. For the analysis of cognitive function, the BACS-scores of each of the six domains will be converted into six separate and a composite Z-score for each participant, controlling for age and gender [48]. Separate repeated measures ANOVAs will be performed for the separate *Z*-scores as dependent variables, time as within factor (baseline and 12 weeks of treatment) and treatment as between factor (raloxifene or placebo). The contrast between raloxifene and placebo at 6 and 12 weeks of treatment will be presented with a 95% confidence interval for the difference between the treatment arms. In addition, post-hoc analyses will be conducted to investigate differences at individual time points. There will be corrected for multiple testing by adjusting the p-values produced by each statistical test for each outcome using the Holm method [49,50].

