#### Additional study parameters

2.8.4

Sex differences and the role of menopausal status in raloxifene efficacy will be explored with regard to the change in positive, negative, general and total symptoms (PANSS) between baseline, 6 weeks and 12 weeks of treatment and change in cognitive function (BACS) between baseline and 12 weeks. These analyses will be performed specifically in the group of patients that received raloxifene treatment, by means of repeated measures ANOVA with time as within factor gender and/or menopausal status as between factor. Furthermore, the analyses on other study parameters, including data from the follow-up visit (6 months after treatment), will be similar to the primary and secondary analyses. With regard to safety data, incidences of key SAEs and AEs will be presented per group. This includes the number and percentage of subjects with at least one occurrence of a SAE or AE. For exploratory purposes, confidence intervals comparing both groups will be provided.

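### The primary analysis is stated in two incompatible forms (mixed model with baseline as covariate; repeated measures ANOVA with baseline as an outcome level), and the deciding test is not named

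*Protocol article*

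**What the plan says.** Section 2.8.2 (Primary study parameters) opens by placing PANSS at weeks 6 and 12 and at 6 months after treatment, and BACS at week 12 and at 6 months, in the primary analysis. It continues: "A mixed model for repeated measurements will be used, including at least time point, treatment group, the interaction between time point and treatment". Further fixed factors are age and sex. The covariates are baseline score, olanzapine-equivalent dose and drug and alcohol use, and there is a random subject intercept.

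The next sentence begins: "More specifically, the primary analysis will be a repeated measures analysis of variance (ANOVA) with time as within factor". The levels of time are then baseline, week 6 and week 12 for PANSS, and baseline and week 12 for the BACS Z-scores. Treatment is the between factor. No covariate and no 6-month visit appear, although age and gender enter the BACS Z-scores when these are constructed.

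The section goes on to promise the between-arm contrast at weeks 6 and 12 with a 95% confidence interval, and labels comparisons at individual time points post hoc. Section 2.8 adds: "Intention-To-Treat analyses will be conducted". Section 2.8.3 carries the repeated measures ANOVA over to the secondary outcomes. Section 2.8.4 says that analyses of other parameters, "including data from the follow-up visit (6 months after treatment), will be similar to the primary and secondary analyses".

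**The concern.** The second description is introduced as a more specific version of the first, but it is not a special case of it. The two differ in what baseline is, which visits enter and which covariates are used. A reader cannot tell which p-value is the primary result for either PANSS or BACS. If this stays open until the data are unblinded, the analysis can be chosen with the results in view.

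There is also a conditional worry. Repeated measures ANOVA in its conventional form works on complete rows, so a patient with a missing visit would be left out. That sits badly with the intention-to-treat statement in section 2.8.

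**Working it through.** **1. The two descriptions side by side (section 2.8.2)**

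| Feature | First description | Second description |
|---|---|---|
| Model | Mixed model, random subject intercept | Repeated measures ANOVA |
| Baseline score | Covariate | Level of the time factor |
| PANSS visits | Weeks 6, 12, and 6 months after treatment | Weeks 0, 6, 12 |
| BACS visits | Week 12, and 6 months after treatment | Weeks 0, 12 |
| Covariates named | Sex, age, baseline, olanzapine-equivalent dose, drug and alcohol use | None |
| Test that decides | Not named | Not named |

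Rows two to five conflict on the face of the text.

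**2. The plan's own sample size**

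Inputs from sections 2.8 and 2.8.1: "a two-sided 0.05 level of significance will be used to declare treatment arms significantly different"; "a medium effect size of 0.57 was assumed"; "with two sided alpha set at 5% and with 80% power, 50 participants in each group have to be evaluated".

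Two-group t-test, noncentrality = d × √(n/2) = 0.57 × √25 = 2.85 on 98 df: power 80.6%. With 49 per arm it is 79.8%, so 50 reproduces. The calculation fits a plain two-group comparison at one time point. It uses neither repeated measures nor baseline adjustment, so it does not show which description was intended.

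**3. What the choice of test does to power**

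Assumptions not in the document: equal variances and equal correlation ρ between visits (compound symmetry), ρ = 0.5 to 0.7; a week-12 effect of 0.57 SD; a week-6 effect of either half (0.285) or all (0.57) of that. n = 50 per arm, two-sided 0.05, no multiplicity adjustment.

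*Week-12 contrast with baseline as covariate.* Effective d = 0.57/√(1 − ρ²); noncentrality = 5 × effective d.
- ρ = 0.5: d = 0.658, noncentrality 3.29, power 90%
- ρ = 0.7: d = 0.798, noncentrality 3.99, power 98%

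*PANSS time-by-treatment interaction (2 and 196 df).* λ = (n/2) × Σ(δ − mean δ)²/(1 − ρ), where δ is the vector of effects at weeks 0, 6 and 12.
- Half effect at week 6: the sum of squares is 2 × 0.285² = 0.16245. λ = 25 × 0.16245/0.5 = 8.12 gives 72%; λ = 25 × 0.16245/0.3 = 13.54 gives 92%.
- Full effect at week 6: the sum of squares is 0.38² + 2 × 0.19² = 0.2166. λ = 10.83 gives 84%; λ = 18.05 gives 97%.

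*BACS interaction (two levels, 1 df).* This is a comparison of week-12 change. Effective d = 0.57/√(2(1 − ρ)).
- ρ = 0.5: d = 0.570, power 81%
- ρ = 0.7: d = 0.736, power 95%

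*PANSS treatment main effect of the ANOVA (1 and 98 df).* Averaging over time includes baseline, where the expected difference is zero. λ = (n/2) × 3 × (mean δ)²/(1 + 2ρ).
- Half effect at week 6: λ = 75 × 0.285²/2 = 3.05 gives 41%; 75 × 0.285²/2.4 = 2.54 gives 35%.
- Full effect at week 6: λ = 75 × 0.38²/2 = 5.42 gives 64% (63.5%); 75 × 0.38²/2.4 = 4.51 gives 56%.

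**4. Incomplete patients, if the ANOVA is fitted on complete cases**

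Section 2.8.1 expects 10% dropout: 110 × 0.10 = 11 patients, leaving 55 × 0.90 = 49.5 per arm. On the plan's own t-test basis that gives 80.2% power. A 20% loss leaves 44 per arm and gives 75.3%.

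Whether exclusion biases the estimate depends on the contrast. In large simulated samples with dropout depending on the week-6 score, the completers' difference in change stayed at −0.57 (true value −0.57). The completers' raw week-12 difference shrank to between −0.29 and −0.51.

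**The case against.** The strongest reply is that the ANOVA wording is shorthand. It follows directly on a mixed model, and some authors call any repeated measures model an ANOVA. If it is fitted by likelihood, incomplete patients stay in. The full protocol or the analysis plan may also settle missing data and covariance. This stands as far as it goes, and it limits the point in several ways:

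- A reader might infer that the plan discards dropouts and so breaches intention-to-treat. The article never says so; it is a property of the conventional method, for example as commonly run in the package named in section 2.8 ("All statistical analyses will be performed using SPSS for Windows (version 25.0.0.2"), which also allows other software. The expected 10% loss is already budgeted in the 110. Section 2.5.1 schedules an early termination visit with priority for the PANSS. That visit limits the loss only if it is mapped to week 12, which is not stated, and it does not replace a missed week 6.
- A reader might infer that the completers' result is necessarily biased. The simulations do not show this for change, which is what the interaction tests. Bias is possible, not established.
- A reader might infer power of only 35 to 41%. That belongs to a treatment main effect, which the plan never names as primary. Its talk of change, of the interaction and of contrasts at weeks 6 and 12 points elsewhere.
- Criticism of the interaction as an omnibus test, or of deletion for a missed week 6, does not apply to BACS. BACS has two levels in the ANOVA and no week-6 assessment.
- Section 2.8.4 need not demote the primary 6-month data. It may refer to follow-up data on other parameters only.

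The shorthand reading does not remove the conflicts over baseline, visits and covariates. These are contradictions within the article rather than details left to another document.

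**Conclusion.** The point holds as a contradiction about the confirmatory analysis of both primary outcomes. That part rests on the text alone and needs no assumption.

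Its size depends on assumed correlations. For ρ between 0.5 and 0.7 under compound symmetry, the baseline-adjusted week-12 contrast has 90 to 98% power. The ANOVA interaction has 72 to 97% for PANSS, depending on how early the effect appears, and 81 to 95% for BACS. Thus the interaction falls below the planned 80% only in part of the range, for PANSS with a gradual effect and the lower correlations. PANSS power would drop to 35 to 64% only if the treatment main effect were taken as the test.

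The conflict with intention-to-treat is conditional on a complete-case ANOVA. The sample size itself reproduces and is not at fault.

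**What to change.** Name one primary analysis in section 2.8.2:

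- **Model:** a likelihood-based mixed model with outcomes at weeks 6 and 12 for PANSS. BACS has only week 12, so the model reduces there to a baseline-adjusted comparison.
- **Terms:** treatment, time, treatment-by-time and baseline score, with sex and age kept in the model.
- **Patients:** all randomised patients with post-baseline data, analysed as randomised. Report by arm the number with none, since they cannot contribute to this model. State how early termination assessments are assigned to a visit.
- **Primary test:** the raloxifene-minus-placebo contrast at week 12, no longer under a post hoc label.

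Delete the repeated measures ANOVA sentences in sections 2.8.2 and 2.8.3, or label them sensitivity analyses. Place the 6-month off-drug visit once, as a secondary analysis. The residual covariance can be left to the statistical analysis plan.

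The cost is wording, to be settled before unblinding. No new data or visits are needed, standard software fits the model, and under the assumptions above the week-12 contrast has at least as much power as the interaction tests.

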## Abstract

Although acute psychotic symptoms are often reduced by antipsychotic treatment, many patients with schizophrenia are impaired in daily functioning due to the persistence of negative and cognitive symptoms. Raloxifene, a Selective Estrogen Receptor Modulator (SERM) has been shown to be an effective adjunctive treatment in schizophrenia. Yet, there is a paucity in evidence for raloxifene efficacy in men and premenopausal women. We report the design of a study that aims to replicate earlier findings concerning the efficacy of raloxifene augmentation in reducing persisting symptoms and cognitive impairment in postmenopausal women, and to extend these findings to a male and peri/premenopausal population of patients with schizophrenia. The study is a multisite, placebo-controlled, double-blind, randomised clinical trial in approximately 110 adult men and women with schizophrenia. Participants are randomised 1:1 to adjunctive raloxifene 120 mg or placebo daily during 12 weeks. The treatment phase includes measurements at three time points (week 0, 6 and 12), followed by a follow-up period of two years. The primary outcome measure is change in symptom severity, as measured with the Positive and Negative Syndrome Scale (PANSS), and cognition, as measured with the Brief Assessment of Cognition in Schizophrenia (BACS). Secondary outcome measures include social functioning and quality of life. Genetic, hormonal and inflammatory biomarkers are measured to assess potential associations with treatment effects. If it becomes apparent that raloxifene reduces psychotic symptoms and/or improves cognition, social functioning and/or quality of life as compared to placebo, implementation of raloxifene in clinical psychiatric practice can be considered.

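### Eleven unranked primary variables, a Holm rule with no stated family, and a sample size that fits one unadjusted test do not fit together

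*Protocol article*

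**What the plan says.** Section 2.8.2 (Primary study parameters) sets out the primary analysis as repeated-measures ANOVAs "with symptom severity (PANSS total, positive, negative or general scores) as dependent variables". For cognition, the six BACS domain scores are "converted into six separate and a composite Z-score for each participant", with separate ANOVAs on the Z-scores. No variable is put first. Multiplicity is to be handled by "adjusting the p-values produced by each statistical test for each outcome using the Holm method".

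Section 2.8 sets the general rule that "a two-sided 0.05 level of significance will be used to declare treatment arms significantly different". Section 2.8.1 bases the sample size on disjunctive power, "which is the probability of finding at least one true intervention effect across all of the outcomes". There "a medium effect size of 0.57 was assumed", described as similar to the effects reported for symptom severity and for cognition, and "with two sided alpha set at 5% and with 80% power, 50 participants in each group have to be evaluated". No number of outcomes, correlation or adjusted alpha is given.

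The Discussion reports the sponsor's meta-analytic effects: 0.57 for total symptoms, 0.32 positive, 0.40 negative, 0.46 general, and no significant effect on cognition.

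**The concern.** Holm controls the familywise error only over a defined set of tests. Here the set could be all 11 variables, or PANSS and BACS separately, or the time points within each variable. When success means at least one effect, every variable that can trigger success has to be inside the controlled set. Otherwise the chance of a false claim exceeds the stated 5%.

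The variables also overlap: the PANSS total contains its three subscales, and the composite summarises the six domains. Pooling all of them therefore spends alpha on near-duplicates and lowers the power of the two summary scores. If the family is left open until results are known, the reported p-values have no known error rate.

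**Working it through.** **Inputs.** Two-sided alpha 0.05 (sections 2.8 and 2.8.1); effect 0.57 and 50 evaluable per arm (section 2.8.1); 4 PANSS + 7 BACS = 11 variables (section 2.8.2); meta-analytic effects as in the Discussion. The article gives no correlations, so these are assumed. Four sets were used, written as (within PANSS, within BACS, between scales): (0.3, 0.3, 0.1), (0.6, 0.4, 0.1), (0.7, 0.5, 0.2), (0.8, 0.6, 0.3), plus the uncorrelated case.

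**1. The plan's own figure.** Two-sample t-test, noncentrality 0.57 × √(50/2) = 2.85, 98 degrees of freedom, alpha 0.05: power 80.6%. At 49 per arm it is 79.8%. So 50 is exactly the size for one test with no multiplicity adjustment.

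**2. Holm separately within PANSS and within BACS.** Each family can spend 5%. The upper bound is 0.05 + 0.05 = 10%. With independent families it is 1 − 0.95² = 9.75%. Simulation (200,000 runs, normal approximation) gives 9.0%, 8.2%, 7.5% and 6.5% for the four correlation sets. Other assumed sets go slightly lower, so roughly 6% to 9%.

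**3. Holm over all 11.** Error is at most 5%. The first-step alpha is 0.05/11 = 0.0045. Power for PANSS total at that step is 48.2% (t) or 50.5% (normal: Φ(2.85 − 2.838)). For 80% power at that alpha the normal formula gives 2 × (2.838 + 0.842)² / 0.57² = 83.3, so 84 evaluable per arm against the stated 50.

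Holm relaxes after each rejection, so the full procedure does better (simulated, 50 per arm, normal approximation):

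| True effects | PANSS total | At least one rejection |
|---|---|---|
| Discussion's PANSS effects, cognition 0 | about 51% | 55% to 76% |
| Discussion's PANSS effects, all BACS 0.57 | about 58% | 89% to above 99% |
| All 11 at 0.57 | about 62% | 92% to above 99% |

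The last column counts any rejection, including a false one on a null variable, so the first row slightly flatters the plan.

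**4. Two other readings.** If Holm runs only across time points within each variable, nothing protects across the 11. Error could reach 1 − 0.95¹¹ = 43% under independence, and 28% to 40% with the assumed correlations. If Holm runs over PANSS total and BACS composite only, error is 5% and first-step power for PANSS total at alpha 0.025 is 71.6% (t). Full Holm gives about 73% when cognition has no effect and 79% when it has 0.57.

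**5. Sensitivity to the count.** If the ANOVAs on the separate Z-scores exclude the composite, the family has 10 members and first-step power is 49% (t) to 52% (normal). The conclusion does not change.

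**The case against.** The strongest reply is that the Holm sentence most naturally means that every p-value from every outcome enters one adjustment. That fits the wording about power across all outcomes in section 2.8.1, and it controls error at 5%. On that reading there is no inflation. Power is also not short by the plan's own measure: the article states disjunctive power, never power for PANSS total, and it assumes 0.57 for cognition as well as symptoms. Under that assumption pooled Holm over 11 exceeds 80%. All of this stands. A reader might infer that the trial misses its stated error rate and power however the rule is read; the documents do not support that.

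Two further inferences go too far. One is that familywise error simply is 10%: that figure is an upper bound, and overlapping scores must be correlated. The other is that the Abstract's sentence "If it becomes apparent that raloxifene reduces psychotic symptoms and/or improves cognition" is a formal success rule. It goes on to social functioning and quality of life, and says only that implementation can be considered.

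It can also be said that an article may leave the Holm family to the SAP. An undefined family alone would not be a finding. But the article does fix the primary variables, the success criterion, the adjustment and the sample size. An SAP could reconcile them only by demoting variables called primary here, or by accepting a power for PANSS total well below the single-test 80% on which the 50 per arm rests.

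**Conclusion.** The point holds as a mismatch between parts of the plan, not as proof that the trial fails its stated 5% and 80%. Each way of treating all 11 variables as primary has a cost. Separate families leave the at-least-one claim above 5% (roughly 6% to 9%, at most about 10%). One pooled family holds 5% but leaves PANSS total at 48% at the first step and about 51% to 62% under full Holm.

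Disjunctive power is adequate only if cognition really responds as assumed. With the effects in the article's own Discussion and none on cognition it is about 55% to 76%.

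These figures rest on 50 evaluable per arm, a two-group comparison on the standardised scale of section 2.8.1, and assumed correlations. A better estimate of the correlations would move the ranges but not the direction.

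**What to change.** In section 2.8.2, name two primary variables, PANSS total and BACS composite Z-score, both at week 12. Apply Holm once across these two at familywise 0.05. Report the PANSS subscales, the six BACS domains, and the week-6 and 6-month contrasts as secondary, with estimates and 95% confidence intervals.

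In section 2.8.1, restate power under that rule at 50 per arm:
- PANSS total: about 72% (first step) to 79% (full Holm, cognition also 0.57).
- At least one of the two, both effects 0.57, assumed correlation 0.1 to 0.3: about 89% to 92%.
- At least one of the two, only PANSS total having an effect: about 74%.

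The change should be made and dated before unblinding. It needs no extra participants, but it does not restore 80% for PANSS total alone, and the text should say so. The subscales and single cognitive domains lose confirmatory status. The primary aim in section 2.1, which is worded in terms of positive, negative and general symptoms, must be aligned.

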#### Secondary study parameters

2.8.3

The analyses on other continuous measures will be similar, but note that the number of time points may differ (see also Table 1). Analyses include repeated measures ANOVA with time as within factor and treatment (raloxifene or placebo) as between factor, with the BNSS, PSP, TALD and EQ-5D-5L and use of healthcare recourses as dependent variables. A cost-utility analysis will be performed by dividing costs (both health and non-health) by the QALYs (measured with the EQ-5D-5L). Since costs usually show a skewed distribution, non-parametric bootstrap analyses will provide additional information on the average costs. Differences in total costs between the raloxifene and placebo groups will be related to differences in QALYs.

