### Aims and objectives

2.1

The primary aim of this study is to investigate whether raloxifene augmentation compared to placebo is effective in reducing positive, negative and general symptoms and in improving cognitive functioning. Symptoms are measured by the positive and negative syndrome scale (PANSS) [40] and cognitive function is measured with the Brief Assessment of Cognition in Schizophrenia (BACS) [41]. The BACS consists of 6 tasks measuring different domains of cognitive functioning: list learning (verbal memory), verbal fluency (categorical instances and letter fluency, verbal fluency/processing speed), digit sequencing (working memory), symbol coding (processing speed), Token Motor Task (motor speed/processing speed), and the Tower of London Test (reasoning and problem solving).

Secondary outcome variables include general functioning, measured with the personal and social performance (PSP) [42]; severity of thought disorder, measured with the Thought And Language Disorder scale (TALD) [43]; health-related quality of life and quality adjusted life years (QALYs), measured with the EQ-5D-5L [31]; use of healthcare and non-healthcare resources, measured with the institute for Medical Technology Assessment's Medical Consumption Questionnaire (iMTA-MCQ) and Productivity Cost Questionnaire (iMTA-PCQ) respectively and depressive symptoms, measured with Beck's Depression Inventory (BDI) [32]. The Brief Negative Symptom Scale (BNSS) [44] is used to measure negative symptoms with a higher sensitivity [44].

Genetic, hormonal, and inflammatory biomarkers are assessed to predict treatment response. DNA-samples are collected in saliva. Serum hormonal biomarkers include for women prolactin, follicle-stimulating hormone (FSH) and 17β-estradiol, and for men prolactin, 17β-estradiol, free-testosterone and sex hormone-binding globulin (SHBG). Inflammation is measured as C-reactive protein (CRP) in serum.

Safety data are evaluated by comparing incidences of key Serious Adverse Events (SAEs) and Suspected Unexpected Serious Adverse Reactions (SUSARs) between groups, e.g. hospitalisations.

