### Trial design and setting

2.2

Using a randomised double-blind placebo-controlled multicentre design, we assess the effect of raloxifene augmentation in patients with schizophrenia. After assessing in- and exclusion criteria (see section 2.4.1, 2.4.2), participants are randomised to either raloxifene or placebo treatment. The study is divided in two phases: (1) a treatment phase of 12 weeks and (2) a follow-up phase 2 years. The treatment phase consists of a baseline visit, a midterm visit (6 weeks post-baseline), and an end-of-treatment visit (12 weeks post-baseline). The follow-up phase consists of one visit (6 months post end-of-treatment visit), and two calls (at 12 months and 24 months post end-of-treatment visit). Study examinations scheduled in the course of the study are listed in Table 1. All assessments are performed by the study team, while the treating psychiatrist remains in charge of overall medical treatment. Participants continue their regular treatment during the trial, including antipsychotic medication. Any changes in treatment are recorded during each study call/visit.

**Table 1 tbl1:** Study procedures.

	Treatment phase				Follow-up phase			
	Visit 1	Call 1	Visit 2	Visit 3	Visit 4	Call 2	Call 3	*
	Baseline	Week 2 of treatment	Week 6 of treatment	End of treatment	Follow-up 6 months**	Follow-up 12 months**	Follow-up 24 months**	Early termination
**Week**	**0**	**2**	**6**	**12**	**38**	**64**	**116**	**-**
Informed consent, in-/exclusion criteria, MINI Plus	**x**							
Medical history, physical examination, presence/regularity of menses	**x**							
Use of concomitant medication	**x**	**x**	**x**	**x**	**x**	**x**	**x**	**x**
Daily functioning and hospitalizations						**x**	**x**	
Dispense study medication	**x**		**x**					
Side effects, compliance		**x**	**x**	**x**				**x**
Blood pressure	**x**		**x**	**x**				**x**
BMI calculation	**x**			**x**				
Smoking/drug/alcohol use	**x**		**x**	**x**				**x**
BACS, EQ-5D-5L, iMTA-MCQ/PCQ	**x**			**x**	**x**			**x**
PANSS, BNSS, TALD, BDI and PSP	**x**		**x**	**x**	**x**			**x**
Blood samples	**x**		**x**	**x**				**x**
DNA (saliva) sample	**x**							

* Early termination visit, performed when a patient prematurely discontinues the study. ** Calculated from end of treatment visit.

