### Study procedures

2.5

During the baseline visit, informed consent is signed and in - and exclusion criteria are checked. The Mini International Neuropsychiatric Interview 5.0.0 is administered to confirm the diagnosis [45]. If the patient is eligible for participation, he or she is randomised and study medication is dispensed. Blood is drawn at several time points to monitor kidney and liver function, lipids and hormone levels (for an overview of all laboratory measures, see Table 2). Furthermore, in WOCBP a pregnancy test is performed during each treatment visit. Two trained experienced researchers interview the patients at each visit using the PANSS and BNSS questionnaires. At all visits, a PSP score is determined and the severity of thought disorder and depressive symptoms is monitored using the TALD and BDI, respectively. Furthermore, side effects are checked and study medication count is conducted during each treatment visit. Cognitive testing, an assessment of quality of life and the use of healthcare and non-healthcare resources is performed at baseline, at end-of-treatment visit (12 weeks post-baseline) and at follow-up visit (6 months post end-of-treatment visit).

**Table 2 tbl2:** Overview of laboratory measures.

	Visit 1	Visit 2	Visit 3	*
	Screening	6 weeks of treatment	End of treatment	Early termination
**Week**	0	6	12	**-**
Kidney function (eGFR, creatinine)	**x**			
Liver enzymes and function (serum bilirubin, γ-GT, AF, ALAT, ASAT)	**x**	**x****	**x****	**x****
Triglycerides, total cholesterol, HDL- and LDL-cholesterol	**x**	**x****	**x**	**x**
CRP	**x**		**x**	**x**
Hormonal biomarkers	**x**		**x**	**x**
***for men:*** prolactin, 17β-estradiol, free testosterone, SHBG				
***for women:*** prolactin, FSH, β-HCG, 17β-estradiol				
β-HCG***	**x**	**x**	**x**	**x**

* performed if a patient prematurely discontinues the study. ** Performed when levels are above the upper limit of normal at baseline. ***Only for WOCBP. LHT, lithium heparin tube; SCT, sodium citrate tube; SST, serum separator tube; eGFR, estimated glomerular filtration rate; ASAT, aspartate aminotransferase; ALAT, alanine aminotransferase; γ-GT, gamma glutamyl transpeptidase; AF, alkaline phosphatase; HDL, high-density lipoprotein; LDL, low-density lipoprotein; CRP, C-reactive protein; APTT, activated partial thrombin time; FSH, follicle stimulating hormone; SHBG, sex hormone-binding globulin; β-HCG, beta-human chorionic gonadotropin

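### Healthcare resource use, an amount over a period, goes through the same repeated measures ANOVA as the rating scales, a less efficient test of an on-drug effect than a baseline-adjusted week-12 comparison

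*Protocol article*

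**What the plan says.** Section 2.8.3 sets the method for the secondary outcomes: "Analyses include repeated measures ANOVA with time as within factor and treatment (raloxifene or placebo) as between factor". Resource use is among the outcomes to be analysed this way; the sentence goes on to list them: "with the BNSS, PSP, TALD and EQ-5D-5L and use of healthcare recourses as dependent variables". The section calls these analyses similar to the primary ones, "but note that the number of time points may differ (see also Table 1").

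Section 2.1 names the instrument: "use of healthcare and non-healthcare resources, measured with the institute for Medical Technology Assessment's Medical Consumption Questionnaire (iMTA-MCQ"), with a companion questionnaire for productivity costs. Section 2.5 gives the schedule: "healthcare and non-healthcare resources is performed at baseline, at end-of-treatment visit (12 weeks post-baseline) and at follow-up visit (6 months post end-of-treatment visit"). Table 1 agrees, with one row, "BACS, EQ-5D-5L, iMTA-MCQ/PCQ", marked at weeks 0, 12 and 38 and at early termination. The recall period of the questionnaires is not stated.

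Section 2.8.3 also plans a cost-utility analysis with a bootstrap for average costs: "Differences in total costs between the raloxifene and placebo groups will be related to differences in QALYs". The Discussion states that a reduction in use of health and non-health resources is expected.

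**The concern.** BNSS, PSP, TALD and EQ-5D-5L can be treated as levels at a visit. Resource use has meaning only with the length of time it covers. The week-0 reading is wholly before drug, the week-12 reading is the on-drug one, and the week-38 reading follows 26 weeks off drug. An effect confined to treatment therefore shows at one level of the time factor only. The ANOVA spreads it over all levels (main effect) or tests it against within-patient changes that carry the full noise of the baseline reading (interaction). The section does not say which of the two effects is the test.

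At stake is a hypothesis that the authors state themselves. A real reduction in use during treatment is more likely to be reported as no effect than it need be with the data already planned.

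**Working it through.** **Inputs from the article.** Readings at weeks 0, 12 and 38 (section 2.5, Table 1); drug taken in weeks 0-12 (section 2.2); 50 evaluable per arm, effect size 0.57, two-sided 5%, 80% power (section 2.8.1). No figure is given for resource use. The article's own sample size reproduces: a two-sample t test with effect 0.57 needs 49.3, so 50 per arm, with power 0.806.

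**Which readings enter?** Two places point towards week 38: the reference to Table 1 in 2.8.3, and the opening of 2.8.2, which includes 6 months after treatment. Two point away: the BACS ANOVA in 2.8.2 uses baseline and week 12 only, although BACS shares the Table 1 row with the resource questionnaires, and 2.8.4 puts follow-up-visit data among additional parameters. Both readings were checked.

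**Weeks 0 and 12 only.** With two levels, the interaction test is the t test on change. With correlation r between readings, the variance of a change is 2(1 - r) and that of the week-12 reading adjusted for baseline is 1 - r². The ratio is 2/(1 + r), which exceeds 1 for every r below 1: 1.54 at r = 0.3, 1.33 at 0.5, 1.18 at 0.7. Borrowing 0.57 SD as the effect, at r = 0.5:
- Change: 0.57 / (1 × √(2/50)) = 2.85; 2.85 - 1.96 = 0.89; power 0.81.
- Adjusted: 0.57 / (√0.75 × √(2/50)) = 3.29; 3.29 - 1.96 = 1.33; power 0.91.

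**Main effect over weeks 0, 12 and 38, equal windows.** A week-12-only effect is averaged to 0.57/3 = 0.19 SD. At r = 0.5 the SD of the three-reading mean is √((1 + 2 × 0.5)/3) = 0.816. Then 0.19 / (0.816 × 0.2) = 1.16; 1.16 - 1.96 = -0.80; power 0.21.

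**Raw amounts over the visit gaps.** If each reading covers the time since the previous visit, a 26-week amount has up to (26/12)² = 4.7 times the between-patient variance of a 12-week amount at a constant weekly rate.

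**Skewed counts.** Simulation assumptions, none from the article except the 50 per arm: gamma-Poisson contacts, mean 0.5 per week, between-patient CV 0.8-1.2, correlation of rates between periods 0.3-0.6, 40% lower use on drug only. Power:

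| Analysis | Interaction | Treatment main effect |
|---|---|---|
| ANOVA, raw 12/12/26-week amounts | 12-28% | 7-12% |
| ANOVA, equal 12-week windows, three readings | 25-63% | 10-20% |
| ANOVA, weeks 0 and 12 only | 27-61% | 17-35% |

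The week-12 reading alone has 47-78%, and the week-12 reading adjusted for baseline 48-86%. Type I error is near 5% throughout, except about 6-7% for the uncorrected interaction on raw amounts. The adjusted comparison was ahead of the interaction at each combination of CV and correlation tried.

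**The case against.** The strongest reply has five parts.

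1. **Recall period and week 38.** A reader might infer that the plan compares 12-week and 26-week amounts as equals. The article does not say so: no recall period is given, a fixed look-back would make the windows equal, and week 38 may not enter. This stands, and the 12-28% row is therefore conditional.

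2. **No bias.** On-schedule patients in both arms have the same period at each visit, so the arm contrast there is not biased. This stands. The issue is efficiency.

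3. **Planned contrasts.** A reader might infer that an on-drug effect is largely lost. Section 2.8.2 plans post-hoc analyses at individual time points, 2.8.3 says the secondary analyses are similar, and the week-12 contrast alone has 47-78% power. Much of the loss would be recovered, though only by a contrast that stands second to the ANOVA. Section 2.8.2 also describes a mixed model with the baseline score as covariate, which might carry over; the ANOVA that 2.8.3 names does not use it.

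4. **Generic efficiency.** With equal windows the gap is the ordinary advantage of baseline adjustment, not a consequence of unequal periods. That is correct. It also depends on the data: in a simulation with normal data, a 0.57 SD effect and three equal windows, the interaction and the adjusted comparison tied at 0.97 when the correlation was 0.7; at 0.3 they had 0.70 and 0.86. Section 2.8.3 itself expects skewed costs, so the count model is the closer guide.

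5. **Early leavers and costs.** A reader might infer that the arm with more drop-out will look cheaper, or that part of the total costs goes unobserved. The first needs raw early-termination readings in the ANOVA and unequal drop-out; the second needs an assumed look-back. The article states neither.

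A condensed article may leave recall windows and costing rules to a fuller document. Their absence is not the finding; the named test is.

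**Conclusion.** The point holds as one of efficiency. The article names a test for resource use that suits levels better than amounts over a period, and it places the pre-drug reading among the outcomes. On each reading of the text, under the skewed-count assumptions, its interaction is weaker for an on-drug effect than the baseline-adjusted week-12 comparison: about 25-63% (equal windows, or weeks 0 and 12 only) or 12-28% (raw 12- and 26-week amounts), against about 48-86%. The main effect is weaker still.

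The absolute figures rest on an assumed contact rate, spread, correlation and 40% reduction, so they show relative loss only. Bias between arms, an effect largely lost, and unequal periods as a fact are not supported. For a secondary outcome with a stated expectation and a nearly free remedy, the change should be made.

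**What to change.** In section 2.8.3, take use of healthcare resources out of the repeated measures ANOVA and write instead:

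- State the period that each questionnaire reading covers.
- Main comparison: arm difference in on-treatment use, from the week-12 reading expressed per week of the period covered, with the week-0 reading as covariate and a bootstrap confidence interval (the section already plans a bootstrap for costs).
- Report the week-38 reading separately as the off-drug period, also per week.

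This costs a paragraph of wording and a little programming, with no new data, visits or patients. The small downside is that weekly rates from short early-termination periods are noisy.
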